### Economic analysis

A detailed health economic analysis plan, including a full specification of the analysis principles and details, will be written prior to the first substantive analysis and approved in advance by the programme steering committee (PSC).

Costs and cost-effectiveness will be compared between groups at the final 12-month follow-up to capture the economic impact over the longest period available. A secondary analysis at the 6-month follow-up will be carried out for consistency with the primary clinical analysis; however, to avoid unblinding the analyst earlier than necessary, this will be carried out after the primary economic analysis has been completed.

The economic perspective will be that of the NHS and personal social services sectors including those provided within the education sector. Health and social care service use will be collected using the CA-SUS at baseline (covering the previous 3 months) and at the 6- and 12-month follow-up points (covering the period since last interview) using the CA-SUS. Service use will be valued using nationally applicable unit costs (NHS Reference Costs and Personal Social Service Research Unit (PSSRU) Costs of Health and Social Care). The intervention will be directly costed taking a bottom-up (micro-costing) approach and using data on direct contacts recorded in clinical records. Indirect (non-face-to-face) time will be estimated using a questionnaire completed by therapists on time spent on different activities in a typical week. Intervention costs will be estimated using information on therapist salaries and working conditions, including relevant overhead costs (capital, managerial, administrative, etc.).

As a result of current limitations in the measurement of health-related quality of life in young children, capable of generating quality-adjusted life years (QALYs) for application in a cost-utility analysis, our primary economic analysis will be a cost-effectiveness analysis using the primary clinical outcome measure (parent-reported SDQ total difficulties score).

A more exploratory secondary economic analysis will consider cost-utility analysis using the CHU-9D to generate QALYs. Parents of all participants will be asked to proxy-complete the CHU-9D on behalf of all young people.

Additionally, self-report health-related quality of life data will be collected for the main parent/carer using the EQ-5D-5L to explore the impact of the intervention on both young people and their carers.

Cost-effectiveness will be assessed using the net benefit approach and following standard approaches [50]. A joint distribution of incremental mean costs and effects for the two groups will be generated using nonparametric bootstrapping to explore the probability that each of the treatments is the optimal choice, subject to a range of possible maximum values (ceiling ratio) that a decision-maker might be willing to pay for an additional unit of outcome gained. Cost-effectiveness acceptability curves will be presented by plotting these probabilities for a range of possible values of the ceiling ratio [51]. These curves are a recommended decision-making approach to dealing with the uncertainty that exists around the estimates of expected costs and expected effects associated with the interventions under investigation and uncertainty regarding the maximum cost-effectiveness ratio that a decision-maker would consider acceptable.

All economic analyses will be adjusted for co-variates in line with the clinical analyses described above, including the stratification variables (age (< 11 versus 11+), primary mental health disorder (anxiety, depression, disruptive behaviour or trauma), presence of autistic spectrum disorder (yes/no), presence of intellectual disability (yes/no) and for the baseline values of the variables of interest (e.g. baseline cost, CHU-9D score, as appropriate).

### Interim analyses {21b}

No interim analyses are planned by the trial team (TT). Regular reports will be provided to the DMEC members.

### Methods for additional analyses (e.g. subgroup analyses) {20b}

Planned subgroup analyses will be conducted to investigate whether the effect of treatment varies between patients with regard to each of the stratification factors. This will be explored by adding an interaction between each of the factors and treatment to the primary outcome analysis model separately.

Potential mediators and moderators will also be explored. Further details on potential factors and the appropriate analysis methods will be considered in the SAP.

### Methods in analysis to handle protocol non-adherence and any statistical methods to handle missing data {20c}

The main analysis will be conducted following the intention-to-treat principle in accordance with the randomised intervention. All patients with outcome data will be included in the analysis. The primary analysis is likelihood based and therefore robust to the assumption of missing at random, but should substantial missing data be encountered, reasons for this will be explored and a sensitivity analysis will be undertaken to investigate the validity of this missing at random assumption. If the missing at random assumption appears reasonable and the loss to follow-up rate is as anticipated, then we would not use multiple imputation. However, this will be considered in detail in the statistical analysis plan (SAP).

### Plans to give access to the full protocol, participant level-data and statistical code {31c}

The Chief Investigators, Clinical Project Manager, Trial Manager, Statistician, Health Economist and Trial Management Team will have full access to the trial data.

## Oversight and monitoring

### Composition of the coordinating centre and trial steering committee {5d} –

The composition and terms of reference of committees are available on request from the Chief Investigators.

#### Trial Team (TT)

The MICE TT will be responsible for the day to day management of the trial, including operational issues and budget management.

#### Coordinating Centre

The CCTU at UCL act as coordinating centre for the trial, providing specialism in trial design, conduct and statistics. CCTU will also be responsible for monitoring activities undertaken on behalf of the sponsor.

#### Programme management group

A programme management group (PMG) assists with developing the design, co-ordination and strategic management of the trial.

#### Programme steering committee

The PSC is the independent group responsible for oversight of the trial in order to safeguard the interests of trial participants. The PSC provides advice to the CI, CCTU, the funder and sponsor on all aspects of the trial through its independent Chair.

### Composition of the data monitoring committee, its role and reporting structure {21a}

The independent data monitoring and ethics committee (DMEC) is the only oversight body that has access to accumulating comparative data. The DMEC is responsible for safeguarding the interests of trial participants, monitoring the accumulating data and making recommendations to the PSC on whether the trial should continue as planned. The membership, frequency of meetings, activity (including review of trial conduct and data) and authority will be covered in the DMEC terms of reference. The DMEC will consider data in accordance with the statistical analysis plan and will advise the PSC through its Chair. The composition and terms of reference of the DMEC are available on request from the Chief Investigators.

### Adverse event reporting and harms {22}

For the purposes of the MICE trial, only serious adverse events will be reported. All serious adverse events (SAEs) occurring during the trial observed by the investigator or reported by the participant, whether or not attributed to the trial treatment will be recorded on the database. Low-grade adverse events that do not meet the seriousness criteria will not be reported, for example a grade 1 or 2 epileptic seizure that does not result in hospitalisation.

Investigators should notify CCTU immediately and within 24 h at the latest of any SAEs occurring from the time of randomisation until 30 days after the participant completes trial treatment. From this point forward, the site will notify the CCTU of SAEs that are considered related to the trial intervention if they become aware of them until end of follow-up.

Participants must be followed up until clinical recovery is complete, or until the event has stabilised. Follow-up should continue after completion of trial treatment and/or trial follow-up if necessary. Follow-up SAE forms (clearly marked as follow-up) should be completed and emailed to CCTU as further information becomes available. Additional information and/or copies of test results, etc., may be provided separately.

Medically qualified staff appointed by the sponsor will review all SAE reports received. The reviewer will complete the assessment of expectedness.

SAEs that are considered to be related to the trial (resulted from administration of any of the research procedures) and unexpected must be reported to the REC and DMEC. If the related and unexpected event is fatal or life threatening, it must be reported within 7 days of becoming aware of the event; other related and unexpected events must be reported within 15 days.

A list of expected occurrences as a result of the trial treatment is as follows:
Significant deterioration in behaviour operationalised as consistent decline for three consecutive weeks, over four measurement time points, of at least 5 points for relevant behaviour based goals (e.g. as a result of an ‘extinction burst’)Significant deterioration in anxiety operationalised as consistent decline for three consecutive weeks, over four measurement time points, of at least 5 points for relevant anxiety-based goals (e.g. as a result of exposure to feared situations)Significant deterioration in mood operationalised as consistent decline for three consecutive weeks, over four measurement time points, of at least 5 points for relevant mood-based goals (e.g. as a result of cognitive challenging)

Where the SAE falls outside of this list, it must be deemed to be unexpected by the clinical reviewer.

CCTU will keep investigators informed of any safety issues that arise during the course of the trial.

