### Intervention description {11a}

#### Assessment-enhanced usual care

Usual care for mental health disorders varies by site but typically includes referral to CAMHS or hospital-based paediatric psychology services (see Fig. 1). This intervention is considered as ‘assessment-enhanced’ usual care since those in this arm will have completed the DAWBA and the results of the DAWBA will be provided as information to the GP, referrer and other clinical team members involved as appropriate (e.g. neurologist or paediatrician).

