MATCH-ADTC involves a weekly phone/online video call with the therapist who carries out the initial face-to-face assessment; parents complete measures at home and email them to the therapist before each session, and strategies are practiced at home. Face-to-face therapy sessions are permitted if clinically indicated or strongly preferred by the family. MATCH-ADTC comprises an average of 16 sessions but there is flexibility as many young people will have multiple mental health disorders whereas others may have one. MATCH-ADTC uses an algorithm to tailor the treatment to each young person’s individual needs and participants with co-occurring mental health disorders can have each of those addressed within the intervention. Those with intellectual disabilities may need to go at a slower pace than others and therefore may require more sessions. The minimum number is expected to be 10 and the maximum number of sessions is 22. The intervention must be completed within a 6-month window. The two booster sessions may be completed outside of this window. Some patients may receive fewer than 10 sessions providing that there is mutual agreement that their goals have been reached. All therapy sessions will be delivered within 6 months of randomisation although booster sessions can occur between 6 and 12 months post-randomisation. Clinical sessions including face-to-face sessions and telephone/online video calls will be audio and/or video recorded to ensure the sessions are delivered consistently. Key content of MATCH-ADTC for depression includes cognitive and problem-solving strategies and scheduling pleasurable activities; anxiety is addressed using exposure techniques; behavioural strategies, delivered through the parents, include one-on-one time, praise, effective instruction-giving, rewards and ignoring unwanted behaviour; trauma is addressed through developing a trauma narrative, exposure and safety planning. Session by session measurement of symptoms and progress towards self-identified goals is also included as part of the intervention.

Children and young people in the MATCH-ADTC arm will also access usual care for the mental health disorder if required as per Fig. 1.

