#### Secondary outcomes

Separate analyses will be performed for outcomes at 6 months and at 12 months.

The timing of the primary effectiveness outcome at 6 months is because we expect to see the maximum benefit of treatment at this time point. However, we will be following up the children and the difference at 12 months is a secondary outcome.

Models for all secondary efficacy outcomes will be adjusted for the stratification factors.

Binary secondary outcomes will be analysed using mixed effects logistic regression, ordinal secondary outcomes with mixed effects ordinal logistic regression, and continuous secondary outcomes with mixed effects linear regression.

Fisher’s exact test will be used to compare the proportion of children with any serious adverse events in the two randomised groups.

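### As described, SAE detection depends on contact that only the MATCH-ADTC arm has weekly, so the between-arm SAE comparison risks detection bias, probably towards apparent harm, even over an identical window

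*Protocol article*

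**What the plan says.** Under Adverse event reporting and harms {22}, the article records "All serious adverse events (SAEs) occurring during the trial observed by the investigator or reported by the participant", whether or not attributed to treatment. Sites notify all SAEs from randomisation until 30 days after trial treatment is completed. After that they notify only related SAEs of which they become aware.

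Contact differs by arm. In the intervention arm, "MATCH-ADTC involves a weekly phone/online video call with the therapist who carries out the initial face-to-face assessment". On session numbers, "The minimum number is expected to be 10 and the maximum number of sessions is 22", with an average of 16 and two boosters that may fall after 6 months. In addition, "Session by session measurement of symptoms and progress towards self-identified goals is also included as part of the intervention". Study setting {9} says therapists are NHS staff in epilepsy services. For the control arm, "Usual care for mental health disorders varies by site but typically includes referral to CAMHS or hospital-based paediatric psychology services". The only trial contacts described for that arm after baseline are the 6- and 12-month assessments, which both arms share and which a blinded researcher carries out (Who will be blinded {17a}). Families, therapists and the study team are not blinded.

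The number of SAEs is a listed secondary outcome. Under Statistical methods, "Fisher’s exact test will be used to compare the proportion of children with any serious adverse events in the two randomised groups". Parents in both arms also report service use "at the 6- and 12-month follow-up points (covering the period since last interview) using the CA-SUS", and Confidentiality {27} gives the research team consented access to hospital records. The article links neither source to SAEs.

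**The concern.** An admission during the treatment period has many occasions to come to light in a MATCH-ADTC family, because a health professional speaks to them about once a week. In a control family the article describes no scheduled trial contact until month 6. If detection rises with contact, a control child's event is less likely to reach the SAE log than the same event in a MATCH-ADTC child. This is a separate matter from the length of the reporting window: two arms followed for the same number of days could still differ in how completely events are found.

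Because only serious events are reported, this is the only adverse-event comparison the article plans. Unequal detection could produce a false harm signal against a psychological treatment. Equally, it could lead a true difference to be dismissed as a reporting artefact.

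**Working it through.** **Inputs from the document.** Total sample 334, allocated 1:1, so 334 / 2 = 167 per arm; two-sided 5% level; Fisher's exact test on the proportion with any SAE. The plan gives no SAE rate or detection rate, so it has no SAE figure to reproduce.

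**Inputs assumed.** No true difference: the same true risk p of any SAE in both arms, over the same window. Detection probability d_M = 0.95 in MATCH-ADTC and d_C in control, with d_C from 0.95 down to 0.50. True risks of 5%, 10%, 20% and 30%.

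**Step 1: expected risk ratio.** The recorded proportion in each arm is p × d. The ratio of recorded proportions is (p × d_M) / (p × d_C) = d_M / d_C. The true risk cancels, and window length does not enter:

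- d_C = 0.90: 0.95 / 0.90 = 1.06
- d_C = 0.85: 0.95 / 0.85 = 1.12
- d_C = 0.75: 0.95 / 0.75 = 1.27
- d_C = 0.60: 0.95 / 0.60 = 1.58
- d_C = 0.50: 0.95 / 0.50 = 1.90

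**Step 2: expected counts at 20% true risk.** MATCH-ADTC: 167 × 0.20 × 0.95 = 31.7 children. Control at 0.90, 0.75, 0.60 and 0.50: 30.1, 25.1, 20.0 and 16.7 children.

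**Step 3: chance of a false significant result.** For two independent binomials with n = 167 and probabilities p × d_M and p × d_C, sum the joint probability of every pair of counts for which the two-sided Fisher p value is below 0.05:

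| Control detection | Risk 5% | Risk 10% | Risk 20% | Risk 30% |
|---|---|---|---|---|
| 95% (equal) | 2.5% | 3.1% | 3.7% | 3.8% |
| 90% | 2.6% | 3.3% | 4.2% | 4.6% |
| 85% | 2.8% | 3.9% | 5.8% | 7.5% |
| 75% | 3.8% | 6.7% | 13.2% | 20.6% |
| 60% | 7.3% | 16.3% | 37.2% | 58.0% |
| 50% | 11.5% | 27.8% | 59.9% | 82.6% |

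At control detection of 75% or lower, nearly all of these false results point towards harm from MATCH-ADTC (for example 13.1 of the 13.2 percentage points at 20% risk and 75% detection).

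**Reading.** A gap of 5 to 10 percentage points changes the error rate little. The effect becomes material when control loses a quarter or more of affected children and SAEs are not rare.

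**The case against.** The strongest objection is that the article names the sources of SAE reports without saying how reports are obtained. A reader might infer that SAEs come to light only when a family volunteers them. The text does not say so: a parent's answer to a direct question at 6 or 12 months is also a participant report. The timeline table is not shown, and the full protocol may specify such a question. This stands, so the point concerns what the article describes and does not establish that nobody asks.

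A reader might also conclude that the comparison is biased as a matter of fact, or that control events stay hidden from the DMEC. Neither is supported. The seriousness criteria (death, life threat, hospitalisation, lasting disability and the like) describe events that are harder to miss than mild ones. All participants are recruited from epilepsy clinics, and hospital records can be consulted with consent. Both arms have the same blinded assessments, and the option to complete some forms online applies to both, so it creates no difference. Unblinded therapists might also under-report, which would act in the opposite direction. Very large detection gaps are therefore less plausible than small ones.

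What remains is that the stated capture rule depends on contact, contact is heavily unequal in an unblinded trial, and a formal test is applied to the result. Nothing in the article makes detection equal.

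**Conclusion.** The concern holds as a risk of detection bias, probably towards apparent harm from MATCH-ADTC, and it would persist over an identical window. It is not shown that the bias exists, and its size cannot be fixed from the document. On the assumptions above (equal true risk, 95% detection under MATCH-ADTC), the apparent risk ratio is 1.06 to 1.12 for gaps of 5 to 10 points, with a false-positive chance of at most 5.8% for true risks up to 20% (7.5% at 30%). It is 1.27 to 1.90 for gaps of 20 to 45 points, where the chance runs from 3.8% to 82.6% depending on the true risk. The figures at the upper end need control to lose 40% to 50% of affected children at true risks of 20% to 30%, and should be read as the edge of the range. The point merits a change because the remedy is cheap and uses data already collected in both arms.

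**What to change.** Add to Adverse event reporting and harms {22} one source of SAEs that works identically in both arms. At the 6- and 12-month assessments, check every hospital admission that a parent reports on the CA-SUS against the SAE log. This assumes the CA-SUS records admissions, which the article does not show; if it does not, use the consented hospital records.

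Complete any missing SAE form for events inside a reporting window defined identically for both arms. That definition must be reconciled with the present rule, which runs to 30 days after trial treatment and then admits only related SAEs. Otherwise the 12-month check would collect events that the rule excludes.

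In Statistical methods, Secondary outcomes, base the Fisher comparison on the reconciled dataset and show separately the events known only through therapy sessions.

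The cost is a cross-check at two time points and some extra forms, with no new visit or questionnaire if the CA-SUS serves. Some events will be found late, beyond the 24-hour notification limit. SAEs without an admission are not reached, nor are families lost to follow-up (the sample size allows for 10%, about 33 of 334). The reported control count may rise.

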#### Secondary outcomes

Revised Child Anxiety and Depression Scale (RCADS) [34]. This 47-item questionnaire is one of the main outcome measures used in the Children and Young People’s Improving Access to Psychological Therapies (CYP-IAPT) Programme. It is included to allow comparison with this national initiative and has parent and child versions, the subscales are reliable (Cronbach *α* .78–.88) and the measure has discriminant, convergent and factorial validity in a clinical sample [35]. For the trial, the parent version will be used for data completeness.Patient Health Questionnaire (PHQ-9) [36]. This is a 9-item measure of depression in adults completed by the parent/carer about their own mental health.Generalised Anxiety Disorder Assessment (GAD-7) [37]. This is a 7-item measure of generalised anxiety disorder, completed by the parent/carer about their own mental health.Hague Seizure Severity Scale (HASS) [38]—this is a parent-report questionnaire which rates carers’ subjective experiences of the severity of their child’s seizures. Items are statements, which are rated on a 4-point scale from most to least severe (e.g. ‘always’, ‘usually’, ‘sometimes’ or ‘never’). Items describe the length, type and outcomes of a seizure—for example ‘how long do the jerks or cramps last during an attack?’Paediatric Quality of Life Epilepsy Module (PedsQL) [39]. The PedsQL measures the impact of epilepsy on quality of life.Number of serious adverse events. Serious adverse events are those that result in death, are life threatening, require hospitalisation or prolong existing hospitalisation, result in persistent or significant disability or incapacity, or result in a congenital anomaly or birth defect or another important medical condition.

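### Two unreconciled SAE rules, one of them tied to a treatment-completion date that controls do not have, leave the observation window for the between-arm SAE test open

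*Protocol article*

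**What the plan says.** All references are to the protocol article.

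- **Recording rule** (Adverse event reporting and harms {22}). SAEs that occur during the trial and are seen by the investigator or reported by the participant, "whether or not attributed to the trial treatment will be recorded on the database". It has no treatment-based end date and applies to both arms.
- **Notification rule** (same section). Sites must notify the trials unit within 24 hours of "any SAEs occurring from the time of randomisation until 30 days after the participant completes trial treatment". The duty then narrows: "From this point forward, the site will notify the CCTU of SAEs that are considered related to the trial intervention". This later duty lasts to the end of follow-up and covers only events that come to the site's attention.
- **Treatment duration** (MATCH-ADTC in addition to usual care). Contact is weekly, with an average of 16 sessions, an expected minimum of 10 and a maximum of 22. Therapy falls within 6 months of randomisation, "although booster sessions can occur between 6 and 12 months post-randomisation".
- **Control arm** (Assessment-enhanced usual care). "Usual care for mental health disorders varies by site but typically includes referral to CAMHS or hospital-based paediatric psychology services". No completion date is defined.
- **Outcome and test.** "Number of serious adverse events" is a listed secondary outcome (Outcomes {12}). Under Statistical methods, Secondary outcomes, Fisher's "exact test will be used to compare the proportion of children with any serious adverse events in the two randomised groups". The sentence gives no window and does not say which of the two rules supplies the data.

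**The concern.** A comparison of the proportion of children with at least one SAE is fair only if both arms are watched for the same length of time and in the same way. The notification rule ends all-cause reporting at a point set by the course of therapy. In the MATCH-ADTC arm that point moves from child to child. In the control arm sites must decide for themselves what completing trial treatment means: never, at 6 months, at 12 months, or some other date. After the cut-off, reporting narrows to events judged related to the intervention, which will in practice come mainly from the arm that received therapy.

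A site that follows the notification rule could reasonably stop submitting unrelated SAEs once the cut-off has passed, even though the recording rule asks for them. Arms with identical SAE rates could then show different proportions. This is the only between-arm safety test that the article states, so a difference in observation time could be read as harm or benefit of the therapy. An analysis plan can choose a window, but it cannot recover events that sites never submitted.

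**Working it through.** The plan states no figure for SAE risk or for the length of the SAE window, so there is none to reproduce.

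**Step 1. End of the notification window in the MATCH-ADTC arm.** Assume weekly sessions without gaps, starting at randomisation, and 30.44 days per month.

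| Course of therapy | Calculation | Months from randomisation |
|---|---|---|
| 10 sessions | (70 + 30) / 30.44 | 3.3 |
| 16 sessions (stated average) | (112 + 30) / 30.44 | 4.7 |
| 22 sessions | (154 + 30) / 30.44 | 6.0 |
| Full 6 months | 6 + 30 / 30.44 | 7.0 |
| Booster near month 12 | capped at last assessment | 12 |

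The last row applies only if boosters count as trial treatment, which the article does not settle. For controls no date can be calculated.

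**Step 2. Effect on the Fisher test if this rule supplies the data.** Inputs: 334 children randomised 1:1, so 334 / 2 = 167 per arm (Sample size {14}; Sequence generation {16a}); two-sided 5% level (Statistical methods {20a}). Assumptions: the same constant SAE hazard in both arms, and a 12-month SAE risk p of 10%, varied from 5% to 30%.

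Hazard per month: h = −ln(1 − p) / 12. For p = 0.10, h = 0.1054 / 12 = 0.00878.

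Risk over m months: 1 − exp(−h·m). At 7 months: 1 − exp(−0.0615) = 6.0%. At 12 months: 10.0%. The spurious difference is 4.0 percentage points and the risk ratio about 0.6.

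The probability that Fisher's test gives p ≤ 0.05, summed exactly over both binomial distributions:

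| Windows (months), one arm v the other | p = 5% | p = 10% | p = 20% | p = 30% |
|---|---|---|---|---|
| 7 v 7 | 2.0% | 2.8% | 3.4% | 3.7% |
| 12 v 12 | 2.6% | 3.1% | 3.7% | 3.8% |
| 7 v 12 | 9.4% | 20.8% | 44.0% | 62% |
| 4.7 v 12 | 21% | 49% | 84% | 96% |
| 4.7 v 7 | 3.6% | 7.8% | 16% | 25% |

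The arms have equal true rates throughout, so every rejection is false. With 167 in each arm, swapping the windows leaves the rejection rate unchanged and reverses the sign. If controls are followed for longer, therapy looks protective; if boosters extend the MATCH-ADTC window while controls stop earlier, therapy looks harmful.

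**Step 3. If the recording rule supplies the data.** Both arms are then observed over the same period and one of the equal-window rows applies: rejection stays below 5% and there is no window bias.

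**The case against.** The strongest reply is that the section states the recording rule first. It covers all SAEs in both arms without regard to attribution, and the sentence about completing treatment governs expedited notification. If the test is run on the database, the windows are equal. This stands, and it limits the finding. A reader might infer that SAEs are collected only up to the treatment-based cut-off, so that the test does compare unequal windows. The article does not support that; it supports only that the test may do so if sites or the analysis follow the notification rule.

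A reader might also infer that the later, related-only reports can come from one arm alone. That is too strong. The same section defines events related to the trial by any of the research procedures, and controls undergo the diagnostic assessment. The article also calls usual care an intervention in places.

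Other points in the plan's favour:

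- The article says that outcomes at 6 and 12 months are analysed separately, and the analysis plan, which is not shown, may fix a window for the SAE test. The participant timeline is not shown either, so SAEs may already be asked about at those assessments.
- Very large rejection rates can be produced by supposing that every treated child stops at 10 sessions, or that every one has a booster at month 12. Those are extremes and are not relied on here.
- Listing the number of SAEs while testing the proportion of children with any is defensible. The count can be described, and the test avoids treating repeat events in one child as independent.

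What remains is that the two rules are not reconciled and that the control cut-off is undefined. The recording rule also depends on events being observed or reported, and MATCH-ADTC families have weekly therapist contact that controls do not, so detection could differ even under that rule.

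**Conclusion.** The concern holds as a moderate one. The article gives two SAE rules that can lead sites to submit different data, and the narrower one ends at a date that varies from about 3.3 months to the 12-month end of follow-up in one arm and is undefined in the other. The between-arm test is tied to neither.

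If the narrower rule governs, 7 against 12 months at an assumed 12-month risk of 10% gives a false rejection rate of about 21% (9–62% for risks of 5–30%), compared with about 3% under equal 7-month windows. These figures rest on an assumed SAE risk, a constant and equal hazard, and one common window within each arm. Size and direction depend on how sites read the rule for controls: at the average course of 16 sessions, the 10% case gives about 8% if controls stop at 7 months and about 49% if they run to 12. The document does not establish that this bias will occur.

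**What to change.** 1. Reconcile the two rules under Adverse event reporting and harms {22}. State that all SAEs, regardless of relatedness, are submitted for every child over one window counted from randomisation and identical in both arms, for example to the 12-month assessment. Expedited 24-hour notification can keep its own rule if it is stated separately and does not decide what is recorded.
2. Ascertain SAEs in the same way in both arms at the existing 6- and 12-month assessments, if this is not already done.
3. Tie the Fisher comparison under Statistical methods, Secondary outcomes, to that window and to the database record.

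The cost is a short amendment, some additional reports of unrelated SAEs later in follow-up and, where not already asked, one added question at two existing assessments. It is best done while data are still being collected, because events not submitted may not be recoverable.
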